## Abstract

**Background:**

The optimal timing to administer a P2Y12 inhibitor in patients presenting with a non-ST elevation acute coronary syndrome remains a topic of debate. Pretreatment with ticagrelor before coronary anatomy is known as a widely adopted strategy. However, there is poor evidence on how this compares with administration of a P2Y12 inhibitor after defining coronary anatomy (i.e., downstream administration). Moreover, there are limited head-to-head comparisons of the two P2Y12 inhibitors—ticagrelor and prasugrel—currently recommended by the guidelines.

**Study design:**

DUBIUS is a phase 4, multicenter, parallel-group, double randomized study conducted in NSTE-ACS patients designed to compare a pretreatment strategy (including only ticagrelor) versus a downstream strategy (including prasugrel or ticagrelor) and to compare downstream prasugrel with downstream ticagrelor. A total of 2520 patients will be randomly assigned to pretreatment with ticagrelor or to no pretreatment. The PCI group of the downstream arm will be further randomized to receive prasugrel or ticagrelor. The two primary hypotheses are that the downstream strategy is superior to the upstream strategy and that downstream ticagrelor is non-inferior to downstream prasugrel, both measured by the incidence of a composite efficacy and safety endpoint of death from vascular causes, non-fatal MI, or non-fatal stroke, and Bleeding Academic Research Consortium (BARC) type 3, 4, and 5 bleedings.

**Conclusions:**

The DUBIUS study will provide important evidence related to the benefits and risks of pretreatment with ticagrelor compared with a strategy of no pretreatment. Moreover, the clinical impact of using downstream ticagrelor compared with downstream prasugrel will be assessed.

**Trial registration:**

ClinicalTrials.gov NCT02618837. Registered on 1 December 2015.

**Supplementary information:**

**Supplementary information** accompanies this paper at 10.1186/s13063-020-04859-1.

## Introduction

Dual antiplatelet therapy (DAPT) including aspirin and a potent P2Y12 receptor inhibitor (prasugrel or ticagrelor) [1, 2] is the current standard of care in patients with non-ST-segment elevation acute coronary syndromes (NSTE-ACS) [3, 4]. In the absence of contraindication, aspirin is routinely administered to all patients as soon as the initial diagnosis is established, irrespective of subsequent management strategy [3]. Conversely, the risk/benefit ratio of the administration of potent P2Y12 receptor inhibitors before coronary anatomy is known (i.e., pretreatment) remains a matter of debate [5–7]. In the ACCOAST trial (A Comparison of Prasugrel at PCI or Time of Diagnosis of Non-ST Elevation Myocardial Infarction) [8], 4033 NSTEMI patients were randomly assigned to receive prasugrel as pretreatment (2 to 48 h before coronary angiography) or to receive prasugrel after angiography, if PCI was planned. Pretreatment with prasugrel did not reduce the 30-day rate of major ischemic events and produced an increase of major or life-threatening bleeding events. Consistently with the observed harm associated to this strategy, current guidelines do not recommend pretreatment with prasugrel in NSTE-ACS (class III, level of evidence B) [1]. To date, there are no head-to-head comparisons between upstream and downstream administration of ticagrelor in NSTE-ACS patients [3]. However, in the PLATO study (A Comparison of Ticagrelor [AZD6140] and Clopidogrel in Patients With Acute Coronary Syndrome) [2], pretreatment with the assigned P2Y12 inhibitor was mandatory per-protocol, and ticagrelor was associated with an early benefit over clopidogrel in invasively managed NSTE-ACS patients irrespective of the timing of angiography [9]. Based on such observations, the European Society of Cardiology (ESC) guidelines have provided divergent recommendations over the years, although most recent guidelines recommend that with class IIa, level of evidence C, pretreatment with ticagrelor be considered as soon as the diagnosis is established [3]. On the contrary, the American College of Cardiology/American Heart Association (ACC/AHA) guidelines are essentially silent on the optimal timing of P2Y12 inhibitor administration and refer to the how the drugs were tested in their pivotal trials [10]. As far as choice of P2Y12 receptor inhibitors in NSTE-ACS patients, both prasugrel and ticagrelor are preferred over clopidogrel when no contraindications are present [3]. Nevertheless, there are no head-to-head comparisons of ticagrelor versus prasugrel specifically in the setting of NSTE-ACS. Recently, 4018 patients with acute coronary syndromes were enrolled in the ISAR-REACT-5 trial (Intracoronary Stenting and Antithrombotic Regimen: Rapid Early Action for Coronary Treatment) and randomized to receive ticagrelor or prasugrel [11]. This trial showed a lower incidence of death, myocardial infarction, or stroke among those who received prasugrel than among those who received ticagrelor, with similar incidence of major bleedings between arms. However, this trial enrolled a mixed population comprising both patients with ST elevated myocardial Infarction and NSTE-ACS. To note, in the subgroup of patients with NSTE-ACS, ticagrelor was to be administered always before angiography, while pretreatment with prasugrel was not allowed. Accordingly, the ISAR-REACT-5 was designed as a comparison of a ticagrelor-based strategy versus a prasugrel-based strategy rather than merely a head-to-head comparison of agents [11]. Currently, guidelines do not provide any specific recommendation in favor of ticagrelor (either upstream or downstream) over prasugrel [1].

Based on such gaps in the evidence, the DUBIUS (Downstream versus Upstream strategy for the administration of P2Y12 receptor Blockers In non-ST elevated acUte coronary Syndromes with initial invasive indication) study was conceived. The primary objectives of this clinical study are (1) to evaluate the impact of a pretreatment strategy based on ticagrelor administration compared to a no pretreatment strategy based on the downstream administration of ticagrelor or prasugrel in a population of NSTE-ACS patients with an indication to undergo invasive evaluation (coronary angiography planned within 72 h from admission) and (2) to evaluate the impact of downstream ticagrelor compared to downstream prasugrel in patients treated by PCI. Study groups will be compared by means of a combined measure of efficacy and safety endpoints (net clinical benefit). In particular, net adverse cardiac events (NACE) will be assessed at 30 days and 12 months. In this paper, we report the study protocol of the DUBIUS study in accordance with the Standard Protocol Items: Recommendations for Clinical Interventional Trials (SPIRIT) guidelines (Additional file 1).

## Methods

### Target population

DUBIUS is a phase 4, prospective, double randomized, active control, parallel arm, multicenter adaptive clinical investigation in a population of NSTE-ACS patients with an indication to undergo initial invasive evaluation, to be conducted at approximately 40 hospitals in Italy, including both academic and non-academic centers. Patients must meet all eligibility criteria (Table 1), including the following: (1) an initial diagnosis of NSTE-ACS (unstable angina or non-ST elevated myocardial infarction), with an onset of symptoms during the previous 24 h and positive troponin-I or troponin-T; (2) an invasive strategy is chosen, meaning that the patient is expected to undergo coronary angiography within 72 h from hospital admission; (3) patient is able to start therapy with a new P2Y12 inhibitor (prasugrel or ticagrelor) or is on a maintenance dose of clopidogrel or ticlopidine and is able to switch to a new P2Y12 inhibitor (prasugrel or ticagrelor); (4) patient is ≥ 18 and < 85 years old. Diagnosis of NSTE-ACS refers to unstable angina or non-ST elevated myocardial infarction (NSTEMI) as previously defined [4]. Exclusion criteria include having contraindications for receiving ticagrelor or prasugrel (e.g., history of stroke or transient ischemic attack, high bleeding risk) and having received a loading dose of a thienopyridine (ticlopidine, clopidogrel, or prasugrel) or a maintenance dose of prasugrel or ticlopidine or ticagrelor within 7 days of entry into the study. An updated list of participating study sites is available online (https://gise.it/studi/gise).

**Table 1 Tab1:** Eligibility criteria

**Inclusion criteria**	• Age ≥ 18 and < 85. • Non-ST elevated acute coronary syndrome (unstable angina, non-ST elevated myocardial infarction), with an onset of symptoms during the previous 24 h and positive troponin-I or troponin-T. • An initial invasive strategy is chosen (the patient is expected to undergo coronary angiography within 72 h from admission). • Subject is able to start therapy with a new P2Y12 inhibitor (prasugrel or ticagrelor) or is on a maintenance dose of clopidogrel or ticlopidine and is able to switch to a new P2Y12 inhibitor (prasugrel or ticagrelor). • Subject is able to verbally confirm understanding of risks and benefits of dual antiplatelet therapy in coronary acute syndromes, and he/she or his/her legally authorized representative provides written informed consent prior to any clinical investigation related procedure, as approved by the appropriate Ethics Committee. • Patient agrees to comply with follow-up evaluations.
**Exclusion criteria**	**General exclusion criteria** • Known hypersensitivity/contraindication to aspirin, clopidogrel, prasugrel, ticagrelor, heparin, or bivalirudin, or sensitivity to contrast media, which cannot be adequately pre-medicated. • Platelet count < 100,000 cells/mm^3^ or > 700,000 cells/mm^3^, or a white blood cell (WBC) count < 3000 cells/mm^3^ within 7 days prior to index procedure. • Shock. • Have severe hepatic impairment defined as Child-Pugh class C. • Pregnant or nursing subjects and those who plan pregnancy in the period up to 3 years following screening (female subjects of child-bearing potential must have a negative pregnancy test done within 28 days prior to enrollment). • Other medical illness (e.g., cancer or congestive heart failure) or known history of substance abuse (alcohol, cocaine, heroin, etc.) as per physician judgment that may cause non-compliance with the protocol or confound the data interpretation or is associated with a limited life expectancy. • Subject is belonging to a vulnerable population (per investigator’s judgment, e.g., subordinate hospital staff or sponsor staff) or subject unable to read or write. • Currently participating in investigational drug or device trial that has not completed the primary endpoint or that clinically interferes with current trial endpoints. Subject must agree not to participate in any other clinical investigation for a period of 3 years following the index procedure, including clinical trials of medication and invasive procedures. Questionnaire-based studies or other studies that are non-invasive and do not require medication are allowed. **Bleeding risk exclusion criteria** • Prior history of hemorrhagic or ischemic stroke, a transient ischemic attack (TIA), or sub-arachnoid hemorrhage. • History of intracranial neoplasm, arteriovenous malformation, or aneurysm. • Have received fibrinolytic therapy within 48 h of entry or randomization into the study. • Have active pathological bleeding or history of bleeding diathesis. • Have clinical findings, in the judgment of the investigator, associated with an increased risk of bleeding. • Have had recent surgery (within 4 weeks of entry into the study) or are scheduled to undergo surgery within the next 2 months. **Prior/concomitant therapy exclusion criteria** • Have received a loading dose of a thienopyridine (ticlopidine, clopidogrel, or prasugrel) or a maintenance dose of prasugrel or ticlopidine or ticagrelor within 7 days of entry into the study. • Are receiving a GPIIb/IIIa inhibitor (eptifibatide, tirofiban, or abciximab). • Are receiving warfarin or other coumarin derivatives. • Are receiving or will receive oral anticoagulation or other oral antiplatelet therapy (except aspirin [ASA]) that cannot be safely discontinued within the next 3 months. • Are receiving daily treatment with nonsteroidal anti-inflammatory drugs (NSAIDs) or cyclooxygenase-2 (COX2) inhibitors that cannot be discontinued or are anticipated to require > 2 weeks of daily treatment with NSAID or COX2 inhibitors during the study. • Concomitant therapy with a strong cytochrome P-4503A inhibitor or inducer.

### Screening for eligibility

In order to achieve an adequate participant enrolment to reach target sample size, the study will include high-volume sites for referral of NSTE-ACS patients. Participating centers are asked to screen each consecutive patient referred for NSTE-ACS for potential enrolment in the DUBIUS trial.

### Consenting and randomization

Investigators of each participating site will be cardiologists or cardiology fellows and will assess eligibility, obtain patient informed consent prior to performing any study procedures, enroll eligible patients, and assign patients to interventions. The informed consent form is reported in Additional file 2. All subjects enrolled will be randomly assigned in a parallel 1:1 fashion to downstream administration strategy of P2Y12 receptor blockers (prasugrel or ticagrelor) or to an upstream administration strategy (only ticagrelor) (Fig. 1). The randomization to the upstream or the downstream arm should occur as soon as possible after admission. The patients of the downstream arm, who will undergo PCI, will be further randomized in a 1:1 fashion to downstream prasugrel versus downstream ticagrelor at the time of PCI. The second randomization (prasugrel versus ticagrelor) will occur after coronary angiography and before the PCI procedure. The allocation sequence of patients into study groups will be computer-generated by a central system located at the coordinating center. Allocation sequence will be concealed to investigators. Investigators will obtain the randomization information of patients enrolled at their site by a dedicated online system (https://redcap.dctv.unipd.it). Enrolled subjects and investigators will not be blinded to study treatments, so unblinding will not occur. In order to avoid imbalances between groups with respect to age, all randomizations will be blocked by age > 75 years or ≤ 75 years. On the consent form, participants will be asked if they agree to use of their data should they choose to withdraw from the trial. Participants will also be asked for permission for the research team to share relevant data with people from the Universities taking part in the research or from regulatory authorities, where relevant. This trial does not involve collecting biological specimens for storage. A centralized online system will be used for randomization. Once randomized, the subjects are considered enrolled in the study and analyzed as the intent-to-treat (ITT) population.

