### Primary and secondary endpoints

The primary hypothesis will be tested comparing study groups in terms of the 30-day incidence of the combined efficacy and safety primary endpoint (NACE). A list of safety and efficacy endpoints is reported in Table 3.

**Table 3 Tab3:** Secondary endpoints

Single digit and composite of death from vascular causes (death from cardiovascular causes or cerebrovascular causes and any death without another known cause), MI, stroke, TIA, severe recurrent ischemia, recurrent ischemia, or other arterial thrombotic event	
Death from any cause	
Any stent thrombosis according to the ARC criteria	
Target vessel revascularization (TVR)	
Target lesion revascularization (TLR)	
NACE (net adverse cardiac events) occurred in the period between admission and coronary revascularization defined as a composite of death from vascular causes (death from cardiovascular causes or cerebrovascular causes and any death without another known cause), non-fatal MI, or non-fatal stroke, and BARC type 2, 3, 4, and 5 bleeding	
Compliance to mandated antiplatelet therapy	
BARC type 2, 3, 4, and 5 bleeding (single digit and composite)	
All TIMI major, major life-threatening, and minor bleeding	
All CABG surgery-related TIMI major, minor, and composite of TIMI major or minor bleeding	
Non-CABG surgery-related TIMI major, minor, and composite of TIMI major or minor bleeding	

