The primary powered hypotheses include (1) superiority of a downstream administration strategy for P2Y12 receptor blockers over the upstream administration and (2) non-inferiority of prasugrel versus ticagrelor in the PCI group of the downstream strategy arm. The study is powered based on the primary endpoint of incidence at 30 days of the combined primary endpoint. For the comparison of upstream and downstream arms, the intent-to-treat (ITT) population will be considered. The study will provide 80% power to establish the superiority of the downstream strategy on the upstream strategy relative to the primary composite endpoint. These calculations are based on the following assumptions: (1) 8% of patients in downstream arm and 11% of patients in the upstream arm (odds ratio = 1.4) having a primary endpoint event within 30 days from randomization, based on extrapolations of previous data. In particular, in patients with NSTE-ACS pretreated with ticagrelor, the 30-day incidence of a composite efficacy endpoint (comprising cardiovascular death, MI, stroke, TIA, or other arterial thrombotic event) was 6.95%, while the rate of major bleeding was 4.05% [19]. In patients with NSTE-ACS not pretreated with a P2Y12 inhibitor, the observed incidence of the composite efficacy endpoint at 30 days (cardiovascular death, MI, stroke) was 7.2%, while the incidence of non-CABG-related TIMI major bleeds was 0.6% and the incidence of all TIMI major bleeds (CABG-related or non-CABG-related) was 1.5% [8]; (2) the time-to-first event analysis based on a 2-sided log-rank test used at a 2-sided significance level (α) of .05 to assess superiority; (3) a dropout rate of about 10%.

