In order to compensate for discrepancies between expected and observed incidence of the primary endpoint, the sample size has been computed using an adaptive approach in three study stages. After each stage, a sample size reassessment will be performed. After having reached the sample size foreseen for each of the three stages, an evaluation using a 95% repeated confidence interval will be used. If the value 0 will be contained in the interval, a sample size reassessment will be performed based on actually observed incidence rates of NACE. Otherwise, data will be passed to the Executive Steering Committee to decide to continue in randomizing patients for the other two analyses or to stop the study. The critical values and the test characteristics of the design were calculated using the Farrington and Manning method [20].

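### Both randomisations are blocked by age above 75, but the primary methods as described do not account for that stratum: a small loss of efficiency that costs nothing to remove

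*Protocol article*

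**What the plan says.** **Randomisation.** The section Consenting and randomization has patients "randomly assigned in a parallel 1:1 fashion" to the upstream or downstream strategy, and randomises downstream PCI patients again, 1:1, to prasugrel or ticagrelor. It then says: "In order to avoid imbalances between groups with respect to age, all randomizations will be blocked by age", above 75 years against 75 or below. The legend of Fig. 1 repeats this for all randomisations.

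**Analysis.** The section Primary and secondary endpoints names three methods:
- For superiority of downstream over upstream, the sample-size assumptions list "the time-to-first event analysis based on a 2-sided log-rank test used at a 2-sided significance level" of 0.05.
- For the three-stage evaluation of the same comparison, a 95% repeated confidence interval is used, and "the test characteristics of the design were calculated using the Farrington and Manning method".
- For prasugrel against ticagrelor, there is a non-inferiority test with a 4-point margin, analysed once at study completion.

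None of the three is described as stratified by age or adjusted for it. None is described as unadjusted either. Age is not mentioned in the analysis text.

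**The concern.** When allocation is balanced within strata of a prognostic factor, the between-stratum part of the outcome variation can no longer contribute to the difference between arms. A standard error computed as if allocation had been unrestricted still includes that part, so it is a little too large. The usual remedy is to analyse by the stratum used at randomisation.

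What is at stake is efficiency and clarity. Intervals for the risk difference are slightly wider than necessary, superiority is slightly harder to show, and the 4-point non-inferiority bound is slightly harder to meet. There is also a reason to settle the choice in writing. Patients and investigators are not blinded, the first comparison is evaluated in stages, and the steering committee sees the interim analyses. The choice between a stratified and an unstratified primary test is best fixed before anyone has seen data.

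**Working it through.** **Inputs from the article.** "A total of 2520 patients will be randomly assigned to pretreatment with ticagrelor or to no pretreatment", so 1260 per arm. The endpoint is the "30-day incidence of the combined efficacy and safety primary endpoint". The assumed rates are "8% of patients in downstream arm and 11% of patients in the upstream arm". The second comparison has 500 per arm, a 4-point margin, anticipated rates of 5% (ticagrelor) and 8.5% (prasugrel), and a true difference of 1 point.

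**Assumptions, not in the article.** The share aged over 75 is f = 15-45%. The event-rate ratio, over 75 against 75 or below, is R = 1.5-3.

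**The plan's own figure first.** The article says: "The study will provide 80% power to establish the superiority of the downstream strategy". With 11% v 8%, two-sided 0.05 and 80% power, the pooled two-proportion formula gives

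n per arm = [1.96√(2 × 0.095 × 0.905) + 0.842√(0.11 × 0.89 + 0.08 × 0.92)]² / 0.03² ≈ 1499.

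That is 2998 in total, or 3332 after 10% dropout. The stated 2520 does not reproduce. With 1260 per arm, power is about 73%.

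**Formulas.** For an arm with overall rate p, the rate at 75 or below is a = p/[1 + f(R − 1)] and the rate over 75 is b = Ra.
- Unstratified variance per patient: p(1 − p).
- Stratified variance per patient: (1 − f)a(1 − a) + f·b(1 − b).
- SE of the difference: √[(sum of the two arms' variances)/n].
- Power: Φ(d/SE − 1.96), where d = 0.03 for superiority. For non-inferiority d = 0.04 − 0.01 = 0.03.

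**One case in full (superiority, f = 0.25, R = 3).**
- Unstratified: (0.0979 + 0.0736)/1260, SE = 0.01167, half-width 2.287 points, power Φ(2.571 − 1.96) = 73.0%.
- Stratified, 11% arm: a = 7.33%, b = 22%, variance 0.0939. 8% arm: a = 5.33%, b = 16%, variance 0.0715.
- Stratified SE = √(0.1653/1260) = 0.01146, half-width 2.245 points, power 74.5%.
- The interval is 1.8% narrower. This is the largest gain in the range examined.

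**Whole range.**

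| Comparison | Half-width, unstratified | Half-width, stratified | Power, unstratified | Power, stratified |
|---|---|---|---|---|
| 11% v 8%, 1260 per arm | 2.287 | 2.245-2.283 | 73.0% | 73.1-74.5% |
| 5% v 6%, 500 per arm | 2.825 | 2.798-2.823 | 54.8% | 54.9-55.6% |
| 7.5% v 8.5%, 500 per arm | 3.362 | 3.313-3.358 | 41.6% | 41.7-42.7% |

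Half-widths are in percentage points. The second comparison is shown at two levels because a 1-point true difference does not fit the anticipated 5% and 8.5% together.

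**The same in patients.** The share of outcome variance explained by age is f(1 − f)(b − a)²/[p(1 − p)], here with p = 9.5%.
- 25% over 75, 17% v 7%: 0.25 × 0.75 × 0.10²/(0.095 × 0.905) = 0.0218. The SE is about 1.1% too large, worth 0.0218 × 2520 ≈ 55 patients.
- 25% over 75, 14% v 8%: 0.0079, worth about 20 patients.

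**Validity.** With no true difference and a rate of 9.5%, the unstratified test rejects with probability about 2Φ(−1.96/ρ), where ρ is the stratified SE divided by the unstratified SE. Over the range ρ runs from 0.982 to 0.999, so the error rate runs from 4.6% to 5.0%. Simulation with 200,000 runs per scenario agrees, and gives about 5.0% for the Mantel-Haenszel test. There is no inflation.

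**The case against.** The strongest objection is that the mismatch is read from silence. The log-rank test appears among the sample-size assumptions, and Farrington and Manning is named for the design calculations. Whether the final test carries the randomisation stratum is often left to the analysis plan, and neither that plan nor the full protocol is shown. This stands in part: the article does not exclude stratification. However, it does fix test, sidedness, significance level and interval level. Its section on deviations treats the preceding text as the statistical plan, with major changes to be made by amendment. Asking for the stratum to be stated is therefore fair. Asserting that the trial will ignore it is not.

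The second objection is that the gain is negligible. It is small, and no plausible conclusion of the trial hangs on it. The argument for acting is that it costs nothing.

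A reader might infer more than the article supports:
- *Age could be imbalanced by chance in the PCI subset.* The prasugrel v ticagrelor randomisation is itself blocked by age within that subset.
- *The stratum separates the prasugrel regimens.* Under Study drugs administration the lower maintenance dose is triggered by age over 75 or by weight under 60 kg, so age marks the regimen only in part. A Mantel-Haenszel estimate also still pools over the strata.
- *The log-rank or hazard-ratio interval would be narrower.* Stratifying there mainly moves the estimate away from the null and gains some power. The interval need not shrink.

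**Conclusion.** The point holds as a minor, free improvement. Both randomisations are blocked by age, and the primary methods as described do not account for that block. For the risk difference the consequence is a valid but slightly conservative analysis. Intervals are about 0.1-1.8% wider than a stratified analysis would give. The power forgone is at most about 1.5 points for the first comparison and about 1 point for the second.

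These figures assume that age is prognostic, with 15-45% of patients over 75 and an event-rate ratio of 1.5-3. The article supplies none of this, so the loss cannot be derived from it alone. If age is not prognostic, nothing is lost or gained.

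Two stronger conclusions would be wrong. The type I error is not inflated. Stratifying also does not rescue the power: at 2520 patients the first comparison moves from about 73% to at most 74.5%, still short of the stated 80%.

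**What to change.** Add one sentence to the analysis text: the primary analyses account for the randomisation stratum (age above 75, or 75 and below), using a Mantel-Haenszel stratified risk difference with its confidence interval for both hypotheses and a stratified log-rank test wherever log-rank is used, with the estimate in each stratum shown. For upstream v downstream this applies at every stage, including the repeated confidence interval. For prasugrel v ticagrelor it applies to the single final analysis.

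If the full protocol or analysis plan already says this, confirming it is enough. The cost is the sentence and a stratum term in the program. The variable is already recorded and used at randomisation, so no new data and no further patients are needed.
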